**Methods:**

The study is a multicenter, randomized, controlled, superiority clinical trial. Participants will be a total of 137 hard-to-treat individuals enrolled in opioid agonist treatment (OAT). Participants will be randomized to either a standard treatment (14 sessions of individual manual-based cognitive behavioral therapy and motivational interviewing (MOVE-I)) or six sessions of ILC followed by nine sessions of MOVE-I. All participants will receive personalized text reminders prior to each session and vouchers for attendance, as well as medication as needed. The primary outcome is retention in treatment. Secondary measures include severity of drug use and days of criminal offending for profit three and nine months post-randomization. A secondary aim is, through a case-control study, to investigate whether participants in the trial differ from patients receiving treatment as usual in municipalities where ILC and MOVE-I have not been implemented in OAT. This will be done by comparing number of offences leading to conviction 12 months post-randomization recorded in the national criminal justice register and number of emergency room contacts 12 months post-randomization recorded in the national hospital register.

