Compared with patients with other substance use disorders, people with opioid use disorders have the highest risk of criminal activity, psychiatric comorbidity, poly-substance use, infections, such as HIV and hepatitis C [10, 11], as well as excess mortality [12, 13] and a high degree of somatic comorbidity [14]. However, this is primarily due to the fact that opioid use disorders represent the most severe end of the substance use disorder spectrum, and while opioid use disorder is associated with antisocial personality traits, this is mostly as part of its overall relationship with a general propensity for substance use disorders [15]. Once opioid use disorder is established, however, criminal offending may be reduced by the provision of medication assisted treatment [16].

The dual burden of using a drug with particularly heavy consequences and externalizing behavior problems may put some patients at very high risk for a range of adverse outcomes. A considerable barrier to benefitting from treatment is staying in contact with the system for a sufficient time; around 30% of patients drop out of psychosocial treatment across types of substances and treatment, and dropout rates are even higher for more disadvantaged patients and treatments that demand time and concentration [17, 18]. Furthermore, a growing body of evidence suggests that patients with externalizing and criminal behavior are particularly hard to retain in treatment and offer relevant help but that improved retention and treatment effects may be associated with substantially lower costs of crime [19, 20]. Thus, improving retention and outcomes for people with externalizing disorders who enroll in OAT is of crucial importance.

One way to improve retention and outcomes is the use of contingency management (CM) in the form of voucher-based reinforcement therapy [21]. However, the evidence base for specially tailored programs to serve the needs of people with opioid use disorder who are high on externalizing problems is extremely limited. A recent narrative review based on a small handful of studies indicated that cognitive behavioral therapy and CM, or milieu therapy alone or in combination with other interventions, have not been differentially effective for patients with opioid use disorder and antisocial personality disorder [22].

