### Clinicians and trial interventions

Clinicians in this trial will be employed by the participating sites as treatment counsellors and will receive training in the two conditions. The clinicians will all be taken from the existing staff at the clinics. During the trial, the counsellors will meet to discuss the implementation of the two conditions and will be supervised. In addition, after each session, the clinician will send in an electronic record to confirm that the patient has attended the session and will have the opportunity to contact the research team about any questions that have emerged. All assessments, as well as treatment planning and treatment sessions in the two conditions will be audio recorded. Randomly selected recordings that involve all counsellors who conduct each of the tested interventions will be coded, using the SBIRT coding system [31] to ensure intervention fidelity and integrity.

All participants will receive text reminders prior to sessions and a voucher worth DKK 200 for every two sessions attended (equal to approximately US$ 30). A session typically lasts around 30–45 min, depending on the client’s patience and ability to maintain concentration. When clients miss a single session without noticing the counsellor, they lose one voucher. Clients who miss three consecutive sessions without notice are discharged from the project, but not necessarily from treatment, and will still be included in the intention-to-treat analysis.

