#### ILC

ILC is a brief, highly structured psychoeducational program targeting impulsive and destructive behaviors. The original manual is available in English (DOI: 10.13140/RG.2.2.27332.01927). In the two first sessions, the focus is on assessment and establishing treatment goals. Following these two sessions, the patient proceeds to six pre-defined sessions, each covering a different topic (see Table 1). Following ILC, participants will receive six of the sessions of MOVE-I. The content of these six sessions will depend on what themes in the MOVE-I manual are deemed relevant at this stage in treatment by the counsellor and the participant.

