**Fig. 1 Fig1:**
[figure not shown]
CONSORT Flowchart

Summaries will be presented as means and standard deviations for variables that are approximately normally distributed, or as medians and interquartile ranges for skewed variables. Categorical variables will be summarized as frequencies and percentages. Transformations will be used when distributional assumptions are not fulfilled for inferential tests on a continuous measure. We will examine and account for the influence of clustering at the site level on the outcomes. All models will adjust for stratification factors and randomized treatment.

The primary analysis will be an intention-to-treat analysis, utilizing all available data from all randomized participants. Retention in OAT will be compared between the two conditions, controlling for sex, age, and time in treatment, using Cox proportional hazards regression. All randomized participants will be analyzed within the treatment arm to which they were originally allocated after randomization, regardless of whether they retained that specific treatment over the course of the trial or not.

Random intercepts will be estimated for site using the shared option in Stata 16. The primary outcome will be analyzed 365 days after the last patient has been randomized, in order to allow sufficient time for dropouts to occur. Secondary outcome analyses will be performed similarly, controlling for baseline values. For sessions attended, a generalized structural equation model will be estimated specifying a Poisson outcome. For severity of drug use, we will estimate a linear regression model with random intercepts for individual patients and sites. This model will control for age and sex and include the interaction between randomization status (ILC versus standard) and assessment wave (baseline, three, or six months).

For number of convictions, we will assess a Poisson, negative binomial, or Poisson or binomial analysis with zero-inflation. The best-fitting model will be selected based on the Bayesian information criterion [39], without regard to the coefficients or which model favors ILC. We will explore the impact of non-engagement with the intervention and loss to follow-up for secondary variables by undertaking exploratory complier adjusted analyses [40]. No interim analyses or formal subgroup analyses are planned.

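### Sessions attended, a supporting measure, gets a Poisson model with no allowance for dispersion among patients within a site: a minor, cheap improvement, to be made once the ILC session schedule is settled

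*Protocol article*

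**What the plan says.** All references are to the Protocol article.

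- **Model for attendance** (Statistical analyses): "For sessions attended, a generalized structural equation model will be estimated specifying a Poisson outcome".
- **Site** (same section): "Random intercepts will be estimated for site using the shared option in Stata 16". Secondary analyses are to be done in a similar way. A patient-level random intercept is named only for severity of drug use.
- **Convictions** (same section), by contrast, get a choice of distributions: "we will assess a Poisson, negative binomial, or Poisson or binomial analysis with zero-inflation", selected by the Bayesian information criterion.
- **Stopping rule** (Clinicians and trial interventions): "Clients who miss three consecutive sessions without notice are discharged from the project".
- **Dropout** (Background), as a general figure and not one for this trial: "around 30% of patients drop out of psychosocial treatment across types of substances and treatment".
- **ILC schedule.** The abstract gives "six sessions of ILC followed by nine sessions of MOVE-I". The ILC section has two opening sessions on assessment and goals, after which "the patient proceeds to six pre-defined sessions, each covering a different topic", and then: "Following ILC, participants will receive six of the sessions of MOVE-I". The Continued counselling section puts the initial course at 14 sessions in both conditions. Table 1 numbers assessment and treatment planning as sessions 1 and 2 of six.
- **Standing of the measure.** Sessions attended is not among the primary or secondary outcomes in the Outcomes section. The time plan in the Appendix lists attendance in the row for other variables.

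**The concern.** A Poisson model takes the variance of the count to equal its mean. Sessions attended out of a fixed course is a bounded count. If most patients attend nearly everything, it varies less than Poisson allows, and the test can miss a real difference in attendance. If some patients leave early or attend much less than others, it varies more, and the test can report a difference that is not there. A site random intercept absorbs differences between sites; it does not describe spread among patients within a site. The article allows for this with convictions but not with attendance.

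What is at stake is a supporting analysis. The Discussion relies on vouchers to keep attendance up in both arms so that non-compliance does not distort the comparison, and attendance is the natural evidence for that. The schedule conflict matters here because the number of sessions offered sets the ceiling on the count in each arm.

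**Working it through.** The article states no figure for this analysis, so there is none to reproduce. From the article: 137 patients (taken as 68 v 69, assuming 1:1) and 14 planned sessions per arm. **Every attendance pattern below is an assumption.**

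**1. Formula.** Let the count have mean μ and variance σ² in both arms, with no true difference. For the log rate ratio, the Poisson variance is (1/μ)(1/n₁ + 1/n₀) and the true variance is about (σ²/μ²)(1/n₁ + 1/n₀). The ratio of true to Poisson standard error is therefore r = √(σ²/μ), and the false-positive rate at a nominal 5% is 2[1 − Φ(1.96/r)].

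**2. Three hand checks, three-miss rule not applied.**
- *Common attendance of 0.9.* σ²/μ = 1 − 0.9 = 0.1, so r = 0.32. False positives are close to 0.
- *30% dropout at evenly spread times (0 to 13 sessions attended), full attendance otherwise.* μ = 0.7×14 + 0.3×6.5 = 11.75. σ² = 0.7×196 + 0.3×58.5 − 11.75² = 16.69. r = √(16.69/11.75) = 1.19; 1.96/1.19 ≈ 1.64; false positives about 10%.
- *Attendance probability uniform across patients.* The count is uniform on 0 to 14: μ = 7, σ² = (15² − 1)/12 = 18.67. r = 1.63; 1.96/1.63 = 1.20; false positives about 23%.

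**3. Effect of the three-miss rule.** The rule covers only misses without notice. Each triple assumes that all / half / none of the misses are without notice, and that the count stops at discharge from the project (20,000 null trials per pattern).

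| Assumed attendance | SE ratio r | Poisson false positives |
|---|---|---|
| 0.9 for all | 0.39 / 0.33 / 0.32 | below 0.1% in all three |
| 0.6 for all | 1.36 / 0.81 / 0.63 | 14.8% / 1.7% / 0.2% |
| Beta(3,1) | 1.37 / 1.04 / 0.95 | 14.9% / 6.1% / 4.2% |
| Beta(1,1) | 2.15 / 1.76 / 1.63 | 36.3% / 26.7% / 22.8% |

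Patient-level robust variance gave 4.6% to 5.4% in all 39 patterns tried.

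**4. Loss of power under uniform attendance.** Take 0.90 v 0.85 for everyone, no rule. The log ratio is ln(12.6/11.9) = 0.057. Poisson SE = √(1/(68×12.6) + 1/(69×11.9)) = 0.049. True SE = √(0.10/(68×12.6) + 0.15/(69×11.9)) = 0.017. The Poisson test needs an estimate beyond 1.96×0.049 = 0.096, which has a probability of about 1%. The robust test has power of about 0.91.

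**5. Site.** With four sites, adding site fixed effects (a stand-in for the random intercept, no true site effect) moved the Poisson false-positive rate by at most 0.2 percentage points. With site differences built in, the Poisson test still rejected 15.9% to 29.9% of null trials in two over-dispersed patterns, against 4.8% to 4.9% with patient-level robust variance and site fixed. Clustering the robust variance on the four sites gave 11.8% to 14.4% over both sets of runs.

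**6. Schedule.**
- ILC section: 2 + 6 + 6 = 14. MOVE-I section: 2 + 3 + 9 = 14. Both agree with Continued counselling.
- Abstract: 6 + 9 = 15 if the six include assessment and planning, as in Table 1; 2 + 6 + 9 = 17 if they do not.
- Table 1: 6 − 2 = 4 topics, against six in the ILC section.

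If one arm were offered 15 sessions and the other 14, identical attendance behaviour would give a rate ratio of about 15/14 = 1.07. In three assumed patterns the robust test then rejected 12% to 93% of the time.

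**The case against.** The strongest reply is about weight. Sessions attended is outside the listed outcomes, has no power calculation, and no objective rests on it. That stands, and it makes the point minor.

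Second, the article names an outcome family and does not rule out robust standard errors; a variance option is detail that a fuller plan could hold. This stands in part. The remedy is compatible with the text. But the same section does set out distributions for convictions and random effects for drug use, so the bare Poisson statement reads as the chosen method, and it can be improved at almost no cost.

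Third, the numbers are assumed. This stands in full. A reader might infer from the larger figures that the attendance test will mislead in a third of trials, or that it has almost no power. The article does not support either. The 36% needs the most varied of the tabulated patterns and every miss to be without notice; the very low power needs all patients to share one attendance probability. With moderate variation (Beta(3,1)) and half or none of the misses without notice, the Poisson rate is 6.1% or 4.2%, near nominal.

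Fourth, under-dispersion depends on a count capped at the planned sessions. The analysis text sets no cap, and counselling may continue after the initial course. That stands, and is a reason to state the counting rule.

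Fifth, the planned random-intercept model was not itself fitted; fixed site effects stood in for it. That limits the site check.

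**Conclusion.** The point holds as a minor improvement. The article specifies a Poisson outcome for sessions attended with no allowance for dispersion within sites, and the resulting standard error can err in either direction. Under assumed patterns the ratio of true to Poisson standard error runs from 0.32 to 2.15. The one case using a dropout figure from the article (30%, a general figure, with even timing assumed) gives about 10% false positives. Neither size nor direction can be known from the document.

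Two further inferences should be resisted. The primary result is not at risk, because retention is analysed by Cox regression and does not use this count. Nor does the schedule conflict show that the arms are offered different numbers of sessions: the ILC, MOVE-I and Continued counselling sections agree on 14, so on the text it is a wording correction to the abstract and Table 1. Table 1 was read from a PDF, but its numbering from 1 to 6 is consistent, and the abstract's conflict does not depend on it.

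**What to change.** 1. **Settle the ILC schedule first.** Align the abstract and Table 1 with the ILC and Continued counselling sections (2 + 6 + 6 = 14). If four topics and nine MOVE-I sessions were intended (2 + 4 + 9 = 15), correct those two sections instead.
2. **State the counting rule.** Count only the planned initial sessions, not continued counselling. If the arms differ in sessions offered, use sessions offered per arm as the exposure or denominator.
3. **Change the variance.** Keep the Poisson mean model, or use fractional or binomial regression for sessions attended out of those offered, with patient-level robust variance and site as a fixed effect. Do not cluster the robust variance on the four sites.

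The cost is one variance option, one counting rule and some wording, with no new data. The one downside is that site fixed effects replace the site random intercept for this analysis alone.

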### Sample size

Sample size was calculated based on the only existing trial [23]. For the primary outcome, retention in treatment, the hazard ratio for the group of patients randomized to ILC compared with treatment as usual was 0.62. We obtained a total sample size of 137 with a power of 80% and an alpha-level of 0.05. We conducted a post hoc power analysis for secondary outcomes (self-reported offending, self-reported substance use). For these measures, we set α = 0.01 due to multiple hypothesis testing and assessed power with three waves of measurement (baseline, three and six months post-randomization) and assumed a correlation of 0.5 between repeated measures. The resulting Cohen’s f that could be measured with a power of 0.95 was 0.16, corresponding to a small to moderate effect size. Finally, for number of offences, we calculated power based on a Poisson distribution; assuming a base-rate of 0.85 offences, the study will have 95% power to measure an incremental risk ratio of 1.43.

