### Randomization

Randomization will be performed by means of the minimization method using Minim randomization software, which is a biased-coin approach with a probability of 0.7 to 0.8 for allocation of the “best fitting” treatment [36]. The minimization method obtains an overall balanced distribution of participants, as the number of expected participants is too small for true randomization. Furthermore, participants will be randomized at each site in order to obtain an equal distribution within each municipality/treatment center. This approach was chosen to (a) reduce the impact of geographical variation between the treatment conditions and (b) reduce the risk of counselors not being able to conduct the treatment type to which they were allocated [37]. The following variables will be used for randomization, all based on patient report:
sexage (dummy coded as 0 if age < 40 years, 1 if age ≥ 40 years).duration of current OAT treatment (four categories: 0–3 months, 4–5 months, 6–12 months, ≥12 months).days of injection drug use in the past month (dummy coded as 0 if 0–9 days, 1 if ≥10).having been employed or studying at least three of the past 6 months.having received a psychiatric diagnosis from a psychiatrist.

After entering the data for an anonymous new patient into a central database, the referring clinician will contact the Center for Alcohol and Drug Research on a telephone number devised for this purpose and will receive a response to randomization.

At the first counselling session after study enrollment, all participants will be assessed using the YouthMap assessment form [38] or the AdultMap assessment form, depending on the age of the participant. The YouthMap and AdultMap assessment forms are comprehensive assessment tools tailored for people in treatment for psychoactive substance use disorders. The AdultMap is almost identical to the YouthMap, with the exception of a few additional items related to any children in the respondent’s care, as well as fewer items related to education. The follow-up assessments will be conducted via telephone interviews at three and nine months post-randomization. The time plan for the study is shown in Table 1 in Appendix.

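### The drug-use severity model assumes equal correlation between all waves; if correlation fades with time, the last-wave change coefficient is tested somewhat too liberally, and an unstructured covariance removes this at almost no cost

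*Protocol article*

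**What the plan says.** The Statistical analyses section of the protocol article gives the covariance for this outcome: "For severity of drug use, we will estimate a linear regression model with random intercepts for individual patients and sites". The model adjusts for age and sex, and the treatment effect enters as arm by wave, with baseline, three months and six months as the waves. The same section says that secondary analyses in general adjust for baseline values. No random slope, residual structure or robust variance is named, and the text does not say which interaction contrast is the test.

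The Sample size section makes the matching assumption. It takes "three waves of measurement (baseline, three and six months post-randomization" and "assumed a correlation of 0.5 between repeated measures". For self-reported offending and substance use it says "we set α = 0.01 due to multiple hypothesis testing", and it reports: "The resulting Cohen’s f that could be measured with a power of 0.95 was 0.16".

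The Randomization section places baseline at the first counselling session and says: "The follow-up assessments will be conducted via telephone interviews at three and nine months post-randomization". The abstract also gives nine months for the last wave, whereas Sample size, Statistical analyses and the Appendix time plan give six.

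**The concern.** The question of interest is whether drug-use severity changes differently in the two arms. The stated model answers it with standard errors that also assume equal variance at each wave and the same correlation between any two waves. One pooled within-patient variance then serves both the early and the late change from baseline.

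The last wave is six or nine months from baseline and the first only three. If correlation weakens with time, the pooled variance is too small for the late change and too large for the early one. The two wave-specific effects would then carry errors of precision in opposite directions: the later one would look more certain than it is, and the earlier one would lose power.

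**Working it through.** **Inputs from the protocol article.** N = 137 in two arms (taken as 68 and 69), three waves, constant correlation 0.5, alpha 0.01 (taken as two-sided), power 0.95, f = 0.16.

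**Input not in the article.** Any fading pattern. Correlations are listed below as baseline–first, baseline–last, first–last.

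**Step 1: reproduce the stated figure.** For the within-between interaction in a repeated-measures analysis, the noncentrality is N·f²·m/(1 − ρ) = 137 × 0.16² × 3 / 0.5 = 21.04, with 2 and 270 degrees of freedom. Power at alpha 0.01 is 0.950, and the f detectable with power 0.95 is 0.1599. The stated 0.16 is reproduced. The between-arm version gives 0.298 and does not match. So the power figure rests on the joint interaction test under equal correlation.

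**Step 2: error rate of a change coefficient.** With complete data and equal variances, the random-intercept model takes the variance of any change as 2σ²(1 − r̄), where r̄ is the mean of the three correlations. The true variance of last minus baseline is 2σ²(1 − r_BL), where r_BL is the baseline–last correlation. Hence

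ratio = (1 − r_BL)/(1 − r̄), actual error = 2[1 − Φ(2.576/√ratio)].

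Example, 0.6/0.3/0.6: r̄ = 0.5, ratio = 0.7/0.5 = 1.4, error = 2.95%. At nominal 0.05 it is 9.8%, so a nominal 95% interval covers about 90%. The first-wave coefficient uses the baseline–first correlation in the same formula: ratio = 0.4/0.5 = 0.8, error = 0.4%.

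**Step 3: a range of patterns, nominal 0.01 (large-sample formula).**

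| Pattern | Last-wave change | First-wave change | Joint 2-df |
|---|---|---|---|
| 0.5/0.5/0.5 (as assumed) | 1.0% | 1.0% | 1.0% |
| 0.6/0.5/0.6 (mild fading) | 1.65% | 0.7% | 1.1% |
| 0.55/0.40/0.55 | 1.9% | 0.7% | 1.1% |
| Autoregressive, 0.5 per 3 months, waves 0/3/6 | 2.3% | 0.5% | 1.2% |
| Autoregressive, 0.5 per 3 months, waves 0/3/9 | 2.1% | 0.2% | 1.3% |
| 0.6/0.3/0.6 | 2.95% | 0.4% | 1.4% |
| Autoregressive, 0.8 per 3 months, waves 0/3/6 | 3.1% | 0.4% | 1.5% |
| 0.4/0.4/0.7 (baseline set apart by mode) | 1.9% | 1.9% | 1.4% |

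Across autoregressive values from 0.3 to 0.9 and both sets of visit times, the last-wave coefficient runs from 1.5 to 3.3% and the joint test from 1.1 to 1.75%. A still milder pattern, 0.55/0.45/0.55, gives 1.6% for the last wave and 0.8% for the first.

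**Step 4: simulation under no arm effect** (137 patients; random intercept for patient; age, sex, arm by wave; four sites as fixed effects; 20,000 trials per pattern).

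| Pattern | Last-wave change | Joint 2-df | Simple last-wave difference |
|---|---|---|---|
| Constant 0.5 | 1.1% | 1.1% | 1.0% |
| Autoregressive 0.5, 0/3/6 | 2.7% | 1.5% | 1.0% |
| Autoregressive 0.5, 0/3/9 | 2.2% | 1.4% | 1.0% |
| Autoregressive 0.5, 0/3/6, 20% lost by last wave | 2.4% | 1.3% | 1.1% |
| 0.6/0.3/0.6 | 3.0% | 1.5% | 1.0% |

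**Step 5: after the change.** With complete data, an unstructured covariance tests last minus baseline with that contrast's own variance. The rate returns to 1.0% for autoregressive correlation of 0.5 and also of 0.7.

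**The case against.** **The test.** The alpha of 0.01 appears in a power calculation that matches the joint interaction test, and that test is only mildly affected. This stands. A reader might infer that the final comparison between arms rejects two to three times too often, or that the strict alpha is lost. The article does not support that. It never names the single last-wave coefficient as the test, the simple last-wave difference shows no excess, and the joint test stays near 1.1 to 1.7%. If baseline is instead a covariate with two later waves, as the general sentence on secondary outcomes could mean, the simulated excess for the last wave is about 1.4 to 1.9 times nominal.

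**The fading.** It is assumed. This also stands: the article gives only a constant 0.5, under which nothing is wrong.

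**The change of mode.** Moving from a session to the telephone does not produce the fading pattern. It would lower baseline's correlation with both follow-ups. With 0.4/0.4/0.7 both change coefficients reject about 2%, and the early one is not conservative. It is a separate reason to doubt equal correlation.

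**The level of detail.** A condensed article may leave residual structure and variance estimator to a fuller plan, and a random intercept with robust standard errors would fit the sentence as written. This stands in part. But the article does choose a specific structure, and the point is that a better one is available, not that detail is missing.

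**Conclusion.** The point holds as a conditional and wave-specific one. The stated random intercepts assume equal variance and one common correlation, and the article supports this only with an assumed 0.5. If correlation fades with time, the last-wave-minus-baseline coefficient rejects about 1.7 to 3% at nominal 0.01, while the first-wave coefficient rejects about 0.2 to 0.8%. The sizes rest on the assumed patterns, equal variances, a two-sided test and, apart from the 20% loss scenario, complete data.

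The conflict between six and nine months must be reconciled, but the conclusion is the same under either. The outcome is secondary and the primary Cox analysis is unaffected, so this is a worthwhile low-cost improvement rather than a serious fault.

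**What to change.** Keep the mean model (age, sex, arm by wave) and the site term. Replace the patient random intercept with an unstructured within-patient covariance over the three waves; in Stata, `mixed` with `residuals(unstructured, t(wave))` and no patient-level constant. Patient-clustered robust standard errors are a second option (1.1 to 1.2% in the fading patterns simulated), but they were checked only with site as fixed effects, so the unstructured covariance is preferable. State one timing for the last wave throughout.

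The cost is one line of specification. Three waves need six covariance parameters (three variances, three covariances) in place of the two for patient and residual variance, which 137 patients can support. If the correlation is in fact constant, the loss of precision is negligible.

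### The drug-use severity model enters baseline as an outcome wave, so it compares change scores and gives up precision that baseline adjustment would keep

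*Protocol article*

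**What the plan says.** All quotations are from the protocol article.

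Under Statistical analyses, a general sentence covers every secondary outcome: "Secondary outcome analyses will be performed similarly, controlling for baseline values". Three sentences later comes the specific model for severity of drug use: "we will estimate a linear regression model with random intercepts for individual patients and sites". Of its covariates the article says "This model will control for age and sex"; baseline severity is not named. The model will also "include the interaction between randomization status (ILC versus standard) and assessment wave (baseline, three, or six months"), so baseline is one of three outcome waves.

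The same section states that "All models will adjust for stratification factors and randomized treatment". An arm main effect is therefore present, and nothing says that the arms share a common baseline mean.

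The Sample size section plans these outcomes in the same form, with "three waves of measurement (baseline, three and six months post-randomization"). It "assumed a correlation of 0.5 between repeated measures", and on the significance level says "we set α = 0.01 due to multiple hypothesis testing".

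**The concern.** Baseline can serve as a covariate that sharpens the comparison at follow-up, or as one of the repeated outcomes. The general sentence suggests the first use and the specific model writes the second. The two are not equivalent. When each arm has its own free baseline mean, the arm-by-wave terms subtract the whole baseline difference between arms. Baseline adjustment subtracts only the part that the correlation between waves supports. Under randomization both target the same effect, but the full subtraction is noisier whenever the correlation is below 1.

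At stake is the width of the interval for a secondary outcome that the abstract names. The Discussion says that few new patients enter the sites, so the lost precision cannot easily be recovered by recruiting more.

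**Working it through.** **Inputs.** From the Sample size section: N = 137, three waves including baseline, correlation ρ = 0.5, α = 0.01, power 0.95, f = 0.16. From Statistical analyses: patient random intercept, arm main effect, arm-by-wave interaction. Assumed here: equal arms, the same variance σ² at each wave, complete data (relaxed in step 5) and no site effect.

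**1. The plan's own figure.** For a repeated-measures within-between interaction with 2 groups and 3 waves:

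- λ = f² × N × m / (1 − ρ) = 0.0256 × 137 × 3 / 0.5 = 21.04
- degrees of freedom 2 and 270
- power at α = 0.01 is 0.950; solving for f at power 0.95 gives 0.1599

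The stated 0.16 reproduces. The between-group version gives 0.298 and does not. The calculation therefore belongs to the arm-by-wave interaction with baseline as a wave.

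**2. What the written model estimates.** In 200 simulated trials of 137 patients with complete data, the arm-by-wave coefficient equalled the arm difference in mean change from baseline to within 4 × 10⁻¹⁵. With baseline added as a covariate and the baseline rows kept, it still equalled that difference (within 6 × 10⁻¹⁵) and the standard error stayed at 0.171. The reason is that the covariate is constant within a patient, while the interaction is a within-patient contrast. Following both sentences literally therefore brings no baseline adjustment.

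**3. Variance at one follow-up wave, per patient.**

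- Change score: 2(1 − ρ)σ² = 2 × 0.5 = 1.00σ²
- Baseline-adjusted: (1 − ρ²)σ² = 1 − 0.25 = 0.75σ²
- Relative efficiency of the written model: (1 + ρ)/2 = 0.75

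Standard error of the arm difference, in units of σ:

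- Written: √(4 × 1.00/137) = 0.171
- Adjusted: √(4 × 0.75/137) = 0.148
- Ratio: √(1/0.75) = 1.155

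The simulated mean standard errors were 0.171 as written, 0.148 with a common baseline mean and 0.148 with baseline as covariate. On this scale 137 patients do the work of 137 × 0.75 ≈ 103. The standardized difference detectable at one wave (α = 0.01, power 0.95) is (2.576 + 1.645) × 0.171 = 0.72 as written and (2.576 + 1.645) × 0.148 = 0.62 with adjustment.

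**4. Sensitivity to the correlation (one wave, complete data).**

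| ρ | Efficiency (1 + ρ)/2 | Variance loss |
|---|---|---|
| 0.3 | 0.65 | 35% |
| 0.4 | 0.70 | 30% |
| 0.5 | 0.75 | 25% |
| 0.6 | 0.80 | 20% |
| 0.7 | 0.85 | 15% |
| 0.8 | 0.90 | 10% |

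For the mean of both follow-ups at ρ = 0.5, efficiency is 0.50/0.75 = 0.67. For the joint two-degree-of-freedom test it lay between 0.67 and 0.89 over the effect patterns tried.

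**5. Sensitivity to missing data.** The missingness rates are assumptions, with data missing at random and ρ = 0.5. The figures are generalized least squares standard errors at one follow-up wave.

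- 30% missing at each follow-up, baseline complete: 0.195 as written and 0.175 under either alternative. The variance gain is 19%.
- 20% of baselines missing as well: 0.208 as written and 0.195 with baseline as covariate and no imputation, a gain of about 12%. The constrained model gives 0.179, a gain of 26%.

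**The case against.** **The specific model governs.** The general sentence covers all secondary outcomes, and a reader would naturally let the detailed model override it. Baseline as a wave is a standard way to take account of baseline. This stands as far as it goes: one might infer a flat contradiction that leaves the estimate open, but following both sentences literally gives the same interaction and the same standard error. It does not remove the loss of precision.

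**Analysis and power calculation agree.** A reader might infer that the power for secondary outcomes is overstated. It is not, because f = 0.16 was computed for this very interaction. A reader might also infer bias. Under randomization the change-score contrast is unbiased. In a single trial it responds more strongly than it should to a chance baseline difference, and that shows up as variance.

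**The size depends on assumptions.** The 25% is on the variance scale, for one wave, at a planning correlation, with complete data. This stands, and steps 4 and 5 show the range. Where the written model already has 95% power at one wave, adjustment raises it only to 98.9%.

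**The baseline may follow allocation.** This is the strongest point. The Randomization section places the YouthMap/AdultMap assessment at the opening counselling session following enrollment. The time plan in the Appendix shows assessment in the post-allocation column for sessions 1–2, although its assessments block appears to list YouthMap at enrollment. Participants and clinicians are not blinded. A common baseline mean is then not guaranteed by randomization alone, and a covariate model without imputation would drop anyone with follow-up data who never attended that session. The change-score model leans on the same baseline, and the ILC and MOVE-I sections give the first two sessions the same focus in both arms. A common baseline is therefore plausible, but the plan has to secure it.

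**This is detail for a statistical analysis plan.** Full parameterisation often is. Here, however, the article itself writes the model form, and that form is the less efficient one.

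**Conclusion.** The point holds as an avoidable loss of precision in a secondary analysis, together with unclear wording on what control for baseline means for this outcome. At the protocol's own correlation of 0.5, with complete data and equal arms, the written model has a standard error about 15% larger than a baseline-adjusted one (0.171 against 0.148). Its variance at one wave is 1.00σ² where 0.75σ² is attainable. The variance loss runs from about 35% at correlation 0.3 to 10% at 0.8. With missing baselines, covariate adjustment without imputation recovers less of it.

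The documents do not support calling the estimate biased or the stated power wrong, and the primary outcome is untouched. The conclusion assumes an arm main effect, which the article states for all models, and a baseline unaffected by allocation, which the article leaves unclear.

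**What to change.** Replace the interaction that includes the baseline wave with one of two forms:

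1. A constrained longitudinal model: all three waves as outcome, one common baseline mean, and arm effects at the follow-up waves only. State that this replaces the separate arm main effect for this outcome. Participants with a missing baseline stay in the analysis.
2. Follow-up waves only as outcome, with arm by wave and the baseline value as covariate. Impute missing baselines so that no randomized participant with follow-up data is dropped.

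State that this is what control for baseline means for drug-use severity.

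Reconcile the timing of the baseline assessment between the Randomization section and the two blocks of the Appendix time plan. If it follows allocation, state that it is completed before arm-specific content begins.

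The cost is a few sentences, plus an imputation step under the second form; no added patients or measurements are needed. The small downside is that both forms depend on a baseline unaffected by allocation, so the timing statement has to accompany the change of model.
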